***Potential Biases***

There may be a chance of selection bias while assigning participants to intervention or control group. To minimize this, a simple randomization technique (Kang et al., 2008) will be used to assign participants to either intervention or control group on 1:1 basis. Concealment of allocation will be done using Sequentially numbered, opaque, sealed envelope (SNOSE) technique (Sil et al., 2019). An open-source random number sequence generator (random.org) will be used to generate random numbers in two columns (77 each) from 1 to 154 indicating column one for intervention group and column two for control group (random.org). The generated numbers in column one and column two will be kept in sequential order in two separate opaque sealed envelopes with a number labelled on outside. A statistician will generate the random number and prepare the envelopes while the research assistant will assign the participants to intervention or control group accordingly.

***Limitations of the study (if any):***

The study is limited to people who are able to use mobile phones therefore may owe to digital literacy bias. The intervention does not allow blinding of the participants and those assessing the outcomes.

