#### Summary of the proposed research protocol (within 200 words)

The overall burden of diabetes is rising, especially in low and middle-income countries such as Nepal. In Nepal, access to diabetes care varies by socio-economic and geographical factors, posing significant challenges to prevention and control. Self-management plays a crucial role in the prevention and control of diabetes. Mobile health (mHealth) technology is increasingly popular for managing chronic diseases, demonstrating its feasibility, acceptability, and effectiveness in enhancing health outcomes and encouraging behavior change. However, its impact on improving self-management among people with type 2 diabetes in Nepal remains unexplored. This randomised controlled trial aims to evaluate a 6-month text based mhealth intervention that support self- management among people with type 2 diabetes in Nepal. The primary outcome includes change in HbA1c at 6 months. Secondary outcomes include behaviour change for diabetes self-management activities, self-efficacy, perceived support, diabetes related stress, quality of life and acceptability of the intervention acceptability. In addition, an economic evaluation will be conducted using a patient perspective. Primary and secondary outcomes will be summarized descriptively, and comparisons will be made using chi-square tests for categorical data and independent sample t-tests for continuous data using SPSS. A cost-effectiveness analysis will be conducted using the incremental cost-effectiveness ratio (ICER).

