A simple randomization technique ([Kang et al., 2008](#_ENREF_29)) will be used to assign participants to either intervention or control group on 1:1 basis. Concealment of allocation will be done using Sequentially numbered, opaque, sealed envelope (SNOSE) technique ([Sil et al., 2019](#_ENREF_46)).An open-source random number sequence generator (random.org) will be used to generate random numbers in two columns (77 each) from 1 to 154 indicating column one for intervention group and column two for control group ([random.org](#_ENREF_41)). The generated numbers in column one and column two will be kept in sequential order in two separate opaque sealed envelopes with a number labelled on outside. The lead researcher will generate the random number and prepare the envelopes while the research assistant will assign the participants to intervention or control group accordingly. A face to face interview will be conducted with people with type 2 diabetes using a structured questionnaire which includes questions related to self-efficacy, perceived support, stress, quality of life, self-care behavior and cost (disease related and development and delivery of intervention) including questions on acceptability of the intervention at follow up. Data will be collected at baseline and 6 months after the intervention.

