Blood pressure: We will use an Omron digital automatic blood pressure monitor with universal sized cuffs to measure blood pressure. Three readings of blood pressure will be taken with an interval of 3 minutes each between the readings after having asked the participant to sit and rest for 15 minutes.

Blood collection There are no specific conditions (fasting, special diets) required for patient. A trained lab person will collect the blood sample using aseptic technique. Laboratory technician and laboratory technologist are responsible for conducting this test and the test will be performed in a laboratory of Dhulikhel hospital. HbA1c test will be performed following standard protocols of the laboratory.

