***Plan for specimen/data management:***

Participants will be assigned unique identifiers or codes to ensure anonymity. No personal identifiers will be revealed beyond the researcher(s) managing the data and it will not be used while reporting the results or sharing data. Confidentiality of the data will be protected in accordance with the requirements of the General Data Protection Regulation (GDPR) and Data Protection Act 2018, University of Huddersfield. Data will be kept confidentially in accordance with the general data requirements of the General Data Protection Regulation (GDPR) and Data Protection Act 2018. All files from data collection will be securely stored in locked cabinet. Electronic data will be initially stored in a password protected laptop and then transferred to one drive at earliest possibility to prevent loss of data. Only limited people directly involved in the study will have access to data. Data will be stored for a period of 10 years and then be safely destroyed. Hard copies having personal identifiers will be kept until entries of data and then will be securely destroyed. Other research related documents such as consent form will be scanned and securely destroyed.

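### The text-message intervention prevents blinding of participants, not of outcome assessors; the protocol gives up masking of the laboratory and partial masking of the follow-up interviewer for a reason that does not hold.

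*Protocol*

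**What the plan says.** Under Limitations of the study, the protocol gives the nature of the intervention as the reason why nobody can be blinded: "The intervention does not allow blinding of the participants and those assessing the outcomes".

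Other sections describe how the outcomes are obtained:

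- **Primary outcome.** The Summary states: "The primary outcome includes change in HbA1c at 6 months". Under Data Collection Tools/ Measures: "Laboratory technician and laboratory technologist are responsible for conducting this test and the test will be performed in a laboratory of Dhulikhel hospital".
- **Coding.** Under Plan for specimen/data management: "Participants will be assigned unique identifiers or codes to ensure anonymity".
- **Secondary scales.** Under Data Collection Procedure: "A face to face interview will be conducted with people with type 2 diabetes using a structured questionnaire". It covers self-efficacy, perceived support, stress, quality of life, self-care and cost, "including questions on acceptability of the intervention at follow up". The cost questions are described as covering the disease and also the development and delivery of the intervention. No order of questions is fixed.
- **Allocation.** In the same section, "the research assistant will assign the participants to intervention or control group accordingly". The interviewer is not named.

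The Potential Biases section deals only with selection bias at assignment. No section provides for masked assessment.

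**The concern.** Whether an assessor can be blinded depends on what the assessor sees, not on whether the participant knows the treatment. A text message goes to the participant's phone. It does not reach the laboratory, and it reaches an interviewer only through what the questionnaire asks or what the participant says. The protocol therefore presents as unavoidable something that is largely a matter of organisation, and a safeguard is dropped for that reason.

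At stake are the psychosocial, quality-of-life and self-care scales. They are answered aloud to an interviewer and compared between arms by t-test at p<0.05. If the interviewer knows the arm, differences in prompting, tone or recording can enter the comparison as an apparent treatment effect. Because this is a positive statement about trial conduct, it is not a detail that a later statistical analysis plan would be expected to supply.

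**Working it through.** **1. Is the stated reason true for each kind of assessor?**

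| Outcome | Who produces the value | What could disclose the arm | Maskable? |
|---|---|---|---|
| HbA1c | Laboratory technician and technologist, by standard laboratory procedure | Nothing in the intervention; only a label or request form that showed the arm | Yes, with ID-only labels |
| Self-efficacy, support, distress, quality of life, self-care | Participant's answers, taken by an interviewer | The interviewer's prior knowledge, or the participant's remarks | Partly |
| Intervention-cost items | Same interview | Possibly the content of the items | Not once they are asked |
| Acceptability | Same interview, follow-up only | The content of the items | Not once they are asked |

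The reason fails for the laboratory. For the interview it fails up to the point at which the arm-revealing items are asked, apart from what participants disclose themselves.

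**2. The plan's own sample size, to fix the number per arm.** Inputs from Sample size determination: mean changes 0.86 (SD 1.08) and 0.18 (SD 1.53), 80% power, 5% significance (two-sided assumed, since sidedness is not stated), 20% attrition.

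- Difference = 0.86 − 0.18 = 0.68.
- Pooled SD = √((1.08² + 1.53²)/2) = 1.324.
- The normal approximation gives 59.5, so 60 per arm. The t-test calculation gives 60.5, so 61 per arm and 122 in total, as stated.
- 122/0.80 = 152.5, so 153, raised to 154 (77 per arm), as stated.

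The stated figures reproduce, and the blinding point does not depend on them. Completers per arm are taken as 61; 77 is the case of no attrition.

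**3. Illustration of what interviewer bias could do.** The documents give no size for it, so the shift b, in SD units, is assumed. With no true effect and n per arm:

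P(p<0.05) = Φ(b√(n/2) − 1.96) + Φ(−b√(n/2) − 1.96)

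| b (assumed) | 61 per arm | 77 per arm |
|---|---|---|
| 0 | 5% | 5% |
| 0.1 SD | 8.6% | 9.5% |
| 0.2 SD | 19.7% | 23.7% |

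For b = 0.1 and n = 61, b√(n/2) = 0.1 × 5.52 = 0.55; for b = 0.2 it is 1.10. More participants do not dilute this kind of bias. They make a false positive more likely.

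**The case against.** The strongest reply is that for most secondary outcomes the real assessor is the participant, who cannot be blinded. A masked interviewer removes only the interviewer's contribution. This stands, and it limits what masking can achieve, but it does not make the sentence true of assessors.

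Three further points stand. HbA1c is an instrument assay at low risk even with an unmasked laboratory. The protocol discloses the absence of blinding openly. The assumed shifts have no support in the documents.

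A reader might also infer more than the text supports:

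- **That the allocator conducts the follow-up interview.** The interviewer is simply not named. Recruitment is planned for July to August 2025 and follow-up for March to May 2026, so overlap is possible but not stated.
- **That the laboratory is told the arm.** No section says so, and the coding already planned makes ID-only labels a small step.
- **That the analyst is unmasked.** The sentence concerns participants and assessors. Masked analysis is commonly left to the statistical analysis plan, which is not shown, so its absence is no finding.
- **That anyone who did not open the envelope is masked.** Data Collection Procedure has the lead researcher generate the sequence and prepare the envelopes, whereas Potential Biases gives that task to a statistician. If the former holds, the lead researcher may know the list without having opened an envelope.

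**Conclusion.** The point holds in a limited form. The protocol is wrong that the intervention prevents blinding of those assessing outcomes; it prevents blinding of participants. The laboratory can be kept unaware of the arm, and the follow-up interviewer can be masked at least in part.

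The gain is mainly less interviewer bias in the self-reported secondary scales. It would be tempting to conclude that the primary result is compromised, or that masking would make the self-reports unbiased. The documents support neither: HbA1c is objective, and participants answer the scales knowing their arm. That reporting bias should remain a listed limitation.

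The rise in the false-positive rate from 5% to about 9% to 20% rests wholly on an assumed shift of 0.1 to 0.2 SD, 61 completers per arm and a two-sided 5% test. It shows what such a bias could do and does not estimate the bias in this trial. The correction is worth making because it costs little.

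**What to change.** 1. Reword the sentence under Limitations so that it says only participants cannot be blinded, and keep participants' own reporting bias as a limitation.
2. Send HbA1c samples and request forms to the laboratory with the study ID only.
3. At follow-up, ask all outcome scales first, and put both the intervention-cost and the acceptability items last.
4. Ask participants at the start not to reveal their arm, and record any unmasking and when it happened.
5. Within existing staff, have the follow-up interview done by someone who neither prepared the allocation list or envelopes nor assigned that participant. Where this is not possible, state that the interviewer was unmasked. To apply this, first settle whether the lead researcher or a statistician prepares the sequence.

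**Cost.** A reordered questionnaire, ID-only labels and a duty roster. The team may be too small for step 5 in every case, which is why the fallback is to report the interviewer as unmasked. Sample size, alpha, power and clinical care are unchanged. The downside is that masking of interviews will be partial.

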***Plan for supervision and monitoring:***

Data collection will be closely monitored by the principal investigator. Data will be checked for completeness and correctness. Data Safety and Monitoring Committee has been formed to report any deviation or inconsistencies during the study.

***Plan for dissemination of the research:***

We will present the results in national and international conferences and publish the findings in the national and international peer-reviewed journals so that findings are accessible to a wide range of audiences.

**Data and Specimen Banking and/or sharing**

NA

**WORK PLAN**

| **S.N.** | **Activities** | **Timeline** |
| --- | --- | --- |
| 1. | Ethical approval | Oct 2024 |
| 2. | Trial registration | Nov 2024 |
| 3. | Formative study | Jan-Feb 2025 |
| 4. | Development of intervention | Mar-Jun 2025 |
| 5. | Recruitment and baseline data collection | Jul-Aug 2025 |
| 6. | Intervention delivery | Sept 2025-Feb 2026 |
| 7. | Follow up data collection | Mar-May 2026 |
| 8. | Data analysis | May-Nov 2026 |
| 9. | Thesis writing | Jul-Dec 2026 |

**ETHICAL CONSIDERATION**

**SIGNIFICANCE OF THE STUDY**

In the resource limited countries like Nepal, mhealth technology can be a cost-effective approach to deliver care and improve the health outcomes. There are studies demonstrating the feasibility, acceptability (Bhandari et al., 2022; Ni et al., 2020) and even effectiveness (Bhandari et al., 2022) of mhealth in improving the health outcomes for hypertension in Nepal (Bhandari et al., 2022; Ni et al., 2020). There is also existing evidence of mhealth as an effective means to communicate health related information and supporting positive behaviour change in a short period of time (Tuitui et al., 2022).

Despite availability of body of evidence on acceptability of mhealth in improving service utilization and health outcomes for chronic conditions, the application of behaviour change interventions through mhealth for self-management of diabetes is yet to be evaluated.

**BALANCE OF RISK AND BENEFIT**

**Risk of the study and Preventive and alleviative measures for risk**

| C2.1. Risk management: | |
| --- | --- |
| **Potential risks identified** | **Proposed measures to mitigate risks** |
| 1. Minimal risk (blood sample collection) | Trained lab person will collect blood sample following standard protocol |
| 2. |  |
| 3. |  |

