Economic evaluation: An economic evaluation will be done of the intervention considering the following aspects: a. Cost (Resource Measurement) The study will measure both direct and indirect costs, including medical expenses (e.g., medication, hospital charges) and non-medical costs (e.g., travel, lost income). These costs will be valued based on actual patient payments and market rates, excluding non-monetized factors like leisure time. b. Cost of the mHealth Intervention Costs associated with the intervention will be calculated using project data, converting monetary values from Nepalese currency to Great Britain Pounds (GBP) at the appropriate exchange rate. Unit costs will be based on actual records. c. User’s Perspective Cost Measurement Out-of-pocket expenses, including medical and non-medical costs, will be collected from participants retrospectively at baseline and prospectively during the study. Participants will record expenses in forms and diaries, which will be used during follow-up data collection. d. Effects Measurement (Health-related Outcomes) The study will assess health outcomes such as HbA1c levels, self-care management, and quality of life using the EuroQol-5 Dimension (EQ-5D) tool. This will help measure Quality-Adjusted Life Years (QALYs), using the Indian EQ-5D value set due to the cultural similarities between Nepal and India. e. Incremental Cost-Effectiveness Ratio (ICER) ICER will measure the economic value of the intervention by comparing the incremental costs and health outcomes (e.g., QALYs gained, HbA1c reduction) between the intervention and control groups.

Acceptability of the intervention will be measured through “Yes” or “No” questions on usefulness, appropriateness, sharing, learning and support in diabetes management and behavior change (Dobson et al., 2016).

Physical measurements

Blood pressure, height and weight will be measured following standard guideline for measurement from WHO STEPS Survey, Nepal (Dhimal M et al., 2019).

Height: Height will be measured using a portable stature meter and values will be recorded in centimetres. We will ensure that the participants removed footwear or any accessories on the head and stands on a flat surface with their feet 10 cm apart and heels against the wall with knees straight.

Weight: Weight is measured using a portable digital seca weighing scale and values will be recorded in kilograms. We will ensure that the participant is on light clothing and without footwear.

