**Benefits of the study**

There is no direct benefit as such however findings from the study help to inform development and effectiveness including acceptability of a text based mhealth intervention. If proven to be effective in improving self-management among people with diabetes, findings can be used to recommend to integrate in routine care to improve self-management for people with type 2 diabetes. Participants involved in the FGDs and IDI will be provided with be provided with expenses for the meal or travel for the day as per Nepalese rate as a form of appreciation of their time. The cost of HbA1c tests for baseline and follow up will be covered from the research.

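### The protocol does not elicit adverse events, low-glucose episodes or hospital admissions in either arm, and its risk table covers only the blood draw

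*Protocol*

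**What the plan says.** Under Balance of Risk and Benefit, the risk table names one risk, "Minimal risk (blood sample collection", with one mitigation, "Trained lab person will collect blood sample following standard protocol". Its other two rows are blank.

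Under Data Collection Procedure, the face-to-face interview holds "questions related to self-efficacy, perceived support, stress, quality of life, self-care behavior and cost", plus acceptability at follow-up. On timing: "Data will be collected at baseline and 6 months after the intervention". Study Variables adds demographics, family history, comorbidity and diabetes complications as participant characteristics. Data Collection Tools/Measures adds EQ-5D, height, weight, blood pressure and the HbA1c sample. The Summary gives HbA1c as primary and then states: "Secondary outcomes include behaviour change for diabetes self-management activities, self-efficacy, perceived support, diabetes related stress, quality of life", followed by acceptability.

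For costing, Data Collection Tools/Measures states: "Out-of-pocket expenses, including medical and non-medical costs, will be collected from participants retrospectively at baseline and prospectively during the study". Medication and hospital charges are among these costs.

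Under Plan for supervision and monitoring: "Data Safety and Monitoring Committee has been formed to report any deviation or inconsistencies during the study".

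On use of the results, Benefits of the study says that, if the intervention proves effective, "findings can be used to recommend to integrate in routine care to improve self-management for people with type 2 diabetes". Expected outcomes of the research makes the same link.

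**The concern.** The only risk considered is venepuncture, which both arms undergo. No possible unintended effect of the messaging programme is named, and no listed item would count events that might differ between arms.

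The trial is meant to lower HbA1c through self-management. Its planning figures are a change of 0.86 with the intervention against 0.18 without (Sample size determination). Selection criteria admit any adult with clinical type 2 diabetes and set no limit by HbA1c or by current treatment. In that setting a reader of the results would want to know whether low-glucose episodes or admissions differed by arm.

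As listed, the plan could report a lower HbA1c together with acceptability and cost, but could not set event counts beside them. A statistical analysis plan that is not shown could not repair this, because it cannot analyse events that nobody asked about.

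**Working it through.** The point rests on what the protocol lists, so the places where event data could appear are taken in turn.

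| Place in the protocol | What it yields | Would it identify a low-glucose episode or admission? |
| --- | --- | --- |
| Study Variables | Comorbidity and complications as participant characteristics | Not described as events counted over follow-up |
| Interview | Scales, cost, acceptability | No such item listed |
| Distress scale, WHOQOL-BREF, EQ-5D | Scores that can worsen | No |
| Weight, blood pressure, HbA1c | Values that can worsen | No |
| Expense forms and diaries | Medication and hospital charges | May point to an admission, but recorded as a cost; the entry need not give the cause |
| Plan for data analysis | Primary and secondary outcomes, cost-effectiveness ratio | No harm outcome |
| Committee | Deviations and inconsistencies | Events not mentioned |

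**The plan's own sample size reproduces.** Inputs from Sample size determination: changes 0.86 (SD 1.08) and 0.18 (SD 1.53), power 80%, level 5% (taken as two-sided), attrition 20%.
- Difference: 0.86 − 0.18 = 0.68.
- Pooled SD: √((1.08² + 1.53²)/2) = 1.324.
- The t-test calculation gives 60.5, so 61 per arm and 122 in total (the normal approximation gives 60 per arm).
- 122/(1 − 0.20) = 152.5, so 153, made 154 for equal arms of 77. With 20% attrition, 77 × 0.80 = 61.6, about 62 completers per arm.

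**What by-arm event data could show at this size.**
- Zero-event upper limit (one-sided 95%), 1 − 0.05^(1/n): 3.8% for n = 77 and 4.7% for n = 62.
- Chance of at least one event among 77, 1 − (1 − p)^77: 54%, 79% and 98% for assumed true risks of 1%, 2% and 5%.
- Power to compare arms, two-sided 5%, normal approximation: Φ[(|p₁ − p₂|√n − 1.96√(2p̄(1 − p̄)))/√(p₁(1 − p₁) + p₂(1 − p₂))]. For 5% versus 10% at n = 77, the numerator is 0.439 − 0.730 = −0.291 and the denominator is 0.371, so z = −0.79 and power is 22%. For 5% versus 15% power is 54%, and for 5% versus 20% it is 81%.

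All event risks here are assumptions; the protocol gives none. The data could bound a risk within an arm, but would seldom settle a difference between arms.

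**The case against.** **Harm is not wholly unmeasured.** A reader might infer that the trial would learn nothing about harm. The protocol does not support that. Distress and quality of life are secondary outcomes compared between groups with confidence intervals, and distress is a plausible harm of a messaging programme. Weight, blood pressure and HbA1c are also measured. This stands, and it limits the point to event elicitation and to the lack of any measure designated as a harm.

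**The mechanism is not in the protocol.** A reader might infer that the messages are known to change eating, activity and medication-taking, and so to provoke low glucose. The list of self-care behaviours in the Background is general. The message content was still to be developed, and the text does not mention low-glucose episodes. So the protocol does not show that the intervention carries this risk. The point needs only that the risk is foreseeable enough to ask about.

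**The committee may see more than its one sentence says.** No charter is shown, so it cannot be said that no safety data reach the committee. What can be said is that its stated remit does not mention such events.

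**The full questionnaire is not shown.** It could hold relevant items, but the protocol's account of it lists none.

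**The recommendation would not rest on benefit alone.** Acceptability, cost, distress and quality of life would be reported too. That is correct; only event counts by arm would be missing.

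**The added data would be weak.** They would be open-label self-report (Limitations of the study says blinding is not possible), and an arm that monitors more may detect more episodes. This stands, and it is why the result should be labelled descriptive.

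**Conclusion.** The concern holds in a limited form. The protocol names only the blood draw as a risk, lists no elicitation of adverse events, low-glucose episodes or admissions in either arm, and gives the committee a stated remit that omits them. The indirect measures could show some worsening but would not reliably identify such events. A routine-care recommendation would therefore lack event data by arm.

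The loss is one of information. With all 77 followed, zero events in an arm would bound its risk at 3.8%; with about 62 completers, at 4.7%. Power to compare arms would be about 22% for an assumed 5% versus 10%. The risk of a text-message programme is probably small, and no figure in the protocol is wrong on this account. This is a cheap improvement worth making; it does not threaten the primary analysis.

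**What to change.** 1. Add to the structured interview, worded identically in both arms and with a fixed recall window: current glucose-lowering treatment; low-glucose episodes, including those needing another person's help; and hospital admissions. If baseline is already complete, add the event items at follow-up. If the questionnaire already holds such items, list them in the protocol.
2. Use the hospital entries in the expense forms and diaries as a second source for admissions.
3. Report counts by arm with exact confidence intervals beside the primary result, labelled descriptive.
4. Extend the remit in Plan for supervision and monitoring so that the committee receives these events, and bring the risk table into line.

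The cost is a few items at visits already planned, one table and short text changes. The downsides are slightly longer interviews, recall error, open-label self-report with possible differential detection if the intervention arm monitors more, and low power to compare arms.
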